**Figure 4 F4:**
[figure not shown]
**Group entry timeline**.

### Usual care control

Patients initially assigned to this condition will be instructed to continue with their on-going medical care. During the control period, these patients will be telephoned or emailed by study personnel to complete the weekly monitoring form (described below) to monitor symptoms, functioning and mood.

## Primary outcomes

**1. *Health Related Quality of Life - Short Form-36 ***(SF-36) [55] is a generic core HRQOL measure yielding an 8-scale profile of functional health and well-being. The SF-36 performs comparatively better than other HRQOL measures in terms of reliability, validity and lightness of respondent/administrative burden [56]. It can be completed in 5-10 minutes and has been used with children as young as 10 years of age [57].

**2. *Pain-related functioning ***will be measured by the ***Pain Disability Index ***(PDI) [58]. The PDI assesses the impact of pain on ability to participate in basic life activities, including social activity, sexual behavior, self-care and life-support activity. The PDI has been used with patients as young as 15 [59]. Good internal reliability (α = .82) and validity have been reported [58,60]. It takes less than 5 minutes to complete.

**3. *Arthritis functioning ***will be assessed with the ***Health Assessment Questionnaire ***(HAQ) [45]. Items include questions about dressing and grooming, rising, eating, walking, hygiene, reaching, grip and activities. The HAQ is one of the most widely recognized measures of patient functioning, with acceptable reliability and validity [45]. It has been used successfully with adolescents as young as 13 years of age [61].

## Secondary outcomes

**1**. ***Disease Activity Scale (DAS) 28 ***is a combined index that measures disease activity in patients with RA and remains a more thorough, established alternative to standard medical exams. This index includes a 28 tender joint count, 28 swollen joint count, Erythrocyte Sedimentation Rate (ESR) and general health assessment using a visual analogue scale. The ESR indirectly measures inflammation in the body and involves collecting blood samples, which will be performed by a qualified phlebotomist.

**2**. ***Pain ***will be measured with a ***numeric rating scale ***(NRS) that asks on a scale of 0 (no pain) to 10 (worst pain possible), what is your current level of pain?

**3**. ***Mood ***will be evaluated using the ***Brief Symptom Inventory 18 ***(BSI-18) [62]. Respondents rate how often they have experienced anxiety, somatization and depressive symptoms within the past 7 days on a 5-point Likert scale ranging from 'Not at all' to 'Extremely.' The BSI-18 has shown adequate to good internal consistency (α range = .74 - .89) and validity [62]. The BSI-18 requires a 6^th ^grade reading ability and takes approximately 4 minutes to complete.

### Exploratory variables

**1. *Blood Pressure and Resting Heart Rate ***will be taken at each medical assessment to evaluate changes in autonomic nervous system activity using a non-invasive, portable, digital blood pressure monitor. A mean blood pressure/resting heart rate value will be derived by taking 2 readings, each 1 minute apart.

**2. *Cytokine Assays ***will be collected from subjects before and after the intervention, at the same time that the blood draws for ESR will be carried out. For the evaluation of pro-inflammatory cytokines, interleukin1-receptor antagonist (IL-1 RA), interleukin-6 (IL-6) and isolated PBMC will be incubated with LPS (500 μl) to yield a final concentration of 5 μg/ml (Ackerman et al., 1998). This dose of LPS has been found to yield optimal production of IL-1, and IL-6 following a 48-hour incubation. Concentrations of these pro-inflammatory cytokines from stimulated cell cultures will be determined by ELISA (R & D Systems). For IL-6, the ELISA intra-assay CV% is 3.1, inter-assay CV% is 2.5, sensitivity <0.7 pg/ml; for IL-1, the intra-assay CV% is 2.3, inter-assay CV% 4.1, sensitivity <1.0 pg/ml. For these assays, we will use high sensitivity kits. The subjects will be brought to a hospital laboratory where a trained phlebotomist will conduct the blood draws needed to assess disease activity in participants. For participants in the intervention group, these blood draws will be performed during a baseline assessment and again at the end of the yoga intervention. Wait-list controls will have their blood drawn at study entry, as well as before and after the yoga intervention.

**3. *Arthritis Self-efficacy Scale ***(ASES) [63] is designed to assess arthritis patients' beliefs that they can perform specific tasks or behaviors to cope with the consequences of chronic arthritis. The scale has 20 items to measure three subscales: pain, function and other symptoms. Reliability is good (α range = .76 - .89). The scale takes approximately 5 minutes to complete.

**4. *Coping Strategies Questionnaire ***(CSQ) [64] is a 42-item checklist measured on a 0-6 Likert scale designed to measure coping in relation to pain. Validity and reliability has been supported in a number of different pain populations, including arthritis patients [64-67]. A child version of the scale (CSQ-C) [34] has been validated and will be used for patients aged 16-20 years. The questionnaire takes approximately 10-15 minutes to complete.

**5**. The ***Chronic Pain Acceptance Questionnaire ***(CPAQ) [68] is a 20-item measure with two subscales: Activity Engagement assessing patients' participation in activities regardless of pain and Pain Willingness, assessing absence of attempts to control or avoid pain. The CPAQ has acceptable reliability (*α*=.78-.82) and validity [68]. It takes approximately 5-10 minutes to complete and is suitable for older adolescents as young as 16 years of age.

**6. *Pittsburgh Sleep Quality Index ***(PSQI) [69] assesses subjective sleep quality over the past month. This 19-item index measures seven components: subjective sleep quality, sleep latency, sleep duration, habitual sleep efficiency, sleep disturbance, use of sleeping medications and daytime dysfunction. Individual component scores or global scores ranging from 0-21 can be evaluated with higher scores indicating poorer sleep quality. The overall reliability coefficient (Cronbach α) is 0.83 and test-retest reliability has a Pearson correlation of 0.85. The index can be completed in less than 5 minutes.

**7. *Functional Assessment of Chronic Illness Therapy Fatigue Subscale ***(FACIT-Fatigue) [70] includes 13 items that assess physical and functional consequences of fatigue. Scores range from 0-52 on a reverse 4-point Likert scale, with higher scores indicating less fatigue. The FACIT-Fatigue has excellent test-retest reliability (*r *= 0.90) and internal consistency (α = 0.93-0.95).

**8. *Mindfulness ***will be assessed using the Five Factor Mindfulness Questionnaire (FFMQ) [71,72], a 39-item self-report measure derived from a factor analysis of items from previously developed mindfulness questionnaires. Items are rated on a Likert scale ranging from 1 ('never or very rarely true') to 5 ('very often or always true'). There are five subscales relating to the five facets of mindfulness: Observe, Describe, Act with Awareness, Nonjudging and Nonreactivity. The FFMQ has been shown to have good internal consistency, with alpha coefficients ranging from .75 to .91, and relationships between the facet scales and other variables are consistent with predictions in most cases. It has been used with high school-aged students previously [73]. It takes less than 10 minutes to complete.

**9. *Medication use ***will be assessed during the patients' weekly phone call/e-mail during which the ***Weekly Monitoring Form ***will be administered. These weekly forms will be used to gather ratings of patients' pain, fatigue, anxiety and depression using 0-10 scales; we will also assess the extent of physical activity during the past week and the extent (i.e., frequency/duration) of any home practice of yoga.

A ***weekly monitoring form ***will include specific questions about functioning, mood, pain, improvement, activity and medication use. The form is an important tool as patients' self-reported functioning will form the basis for understanding the action of yoga over time on symptoms. Thus, responses to the form will be used to determine the minimum and maximum number of yoga sessions needed to produce change. For participants who prefer completing this form online, an online link will be sent to them each week. Otherwise, the form will be telephone-administered by a trained research assistant once a week for two weeks preceding the intervention to ascertain baseline functioning, and then once a week during the intervention and control periods.

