#### The hypotheses to be tested are

**1**: The IYP will be safe, acceptable and feasible: at least 80% of subjects will complete the IYP.

**2**: Following the IYP, participants will show significant improvement on the primary outcomes of general functioning, arthritis functioning and HRQOL relative to controls. The benefits will be apparent post-treatment and at two-month follow-up.

**3**: Following the IYP, participants will report significant improvement on the secondary outcomes of pain, DAS28, and mood compared to controls. These improvements will be evident at both post-treatment and at two-month follow-up.

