### Design

A randomized control trial (RCT) design will be used to examine the impact of IYP for adolescents and young adults aged 16-35 years with RA on the primary outcomes of general and arthritis-specific functioning, and the secondary outcomes of DAS28, pain and mood.

The overall design of the study is depicted in Figure 2 below. After participants have completed the telephone screening and meet the study's eligibility criteria, they will be randomized into the IYP or usual care control group. All participants will be asked to fill out consent forms before their initial medical assessment, which includes a phlebotomy, measurement of blood pressure/resting heart rate, and a joint count conducted by a physician who will be kept unaware of group assignment. Before the medical assessment, a research assistant will send a link to the questionnaires for participants who choose to complete them online. A hard copy of the questionnaires will be taken to the medical assessment if the participant chooses to complete the paper-based version in a private medical office.

Those assigned to the IYP will then engage in the 6-week program; they will repeat the baseline assessments immediately following treatment and again at a two-month follow-up. Patients initially assigned to the wait-list group will continue their usual care. Both the yoga and control groups will either receive weekly phone calls or e-mails to monitor symptoms, medication use and physical activity. After 6 weeks, control participants will be re-assessed to ensure that they still meet study eligibility criteria; those that continue to meet criteria will then take part in the IYP. Following the IYP, participants will then repeat the baseline assessments at post-treatment and two-month follow-up.

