### Secondary analyses

To test ***Hypothesis 3***: Participants in the IYP will report significantly less pain, improved joint count, and mood compared to controls. The same methods used for the primary analyses will be used for the secondary analyses on pain intensity (averaged across the weekly NRS ratings taken during the initial 6-week IYP/control period) and mood. Consistent with ***Hypothesis 3***, we expect that the yoga group will evidence greater improvements on these measures over the 6-week treatment period relative to controls. We will also conduct similar within-group repeated measures analysis, as described in the primary analyses above, to examine changes in the secondary measures from baseline to post-treatment and follow-up. Consistent with ***Hypothesis 3***, we also expect that benefits will be maintained over the two-month follow-up period.

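### Hypothesis 3: the protocol sections disagree on the disease-activity and pain endpoints, and on whether ESR is drawn at two months

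*Protocol article*

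**What the plan says.** All references are to the protocol article.

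- **Hypothesis.** Hypothesis 3 states that "participants will report significant improvement on the secondary outcomes of pain, DAS28, and mood compared to controls". It adds: "These improvements will be evident at both post-treatment and at two-month follow-up".
- **Endpoint definitions.** Secondary outcomes builds DAS28 from four components: tender joints, swollen joints, ESR and a general-health visual analogue scale. Pain is a single 0 to 10 rating in answer to "what is your current level of pain". Mood is the BSI-18.
- **Analysis.** Secondary analyses restates Hypothesis 3 with a joint count where DAS28 stood. It applies the primary-outcome methods to "pain intensity (averaged across the weekly NRS ratings taken during the initial 6-week IYP/control period) and mood". A later sentence extends the within-group repeated-measures analysis to the secondary measures in general, from baseline to follow-up.
- **Blood draws.** Under Exploratory variables, the cytokine paragraph says that cytokine samples are taken together with the ESR draws, and it describes the draws as those needed for disease activity. For the yoga arm, "these blood draws will be performed during a baseline assessment and again at the end of the yoga intervention". The wait-list arm is drawn at study entry, before yoga and after yoga.
- **Visits.** Under Design, the initial medical assessment includes phlebotomy and a joint count. Of those assigned to yoga it says "they will repeat the baseline assessments immediately following treatment and again at a two-month follow-up", and it gives the wait-list arm the same repeats after its own yoga course.
- **Weekly form.** It runs for two weeks before the intervention "and then once a week during the intervention and control periods".

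**The concern.** A secondary hypothesis should carry the same endpoint from its statement through its definition, visit schedule and analysis. Here two of the three endpoints change on the way.

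For disease activity, a reader cannot tell whether the between-group test will be done on DAS28, on a joint count, or not at all. Staff who take the draw schedule from the cytokine paragraph would collect no blood at two months, and a missed draw cannot be recovered later.

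For pain, the outcome section and the analysis section describe two different variables. Either could be defended as the pain endpoint, so the choice could be made after the data are seen. The averaged version also does not fit the baseline, post-treatment and follow-up structure that Secondary analyses takes over from Primary analyses.

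**Working it through.** No figure in the plan bears on this point, so the check is a comparison of the sections.

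| Endpoint | Hypothesis 3 | Secondary outcomes | Between-group analysis | Two-month data |
|---|---|---|---|---|
| Disease activity | DAS28 | DAS28, ESR required | Restated as joint count; not named among the analysed outcomes | Design: phlebotomy repeated. Cytokine paragraph: no draw |
| Pain | Pain | One current rating | Mean of weekly ratings over six weeks | Single rating implied by Design; weekly mean: none stated |
| Mood | Mood | BSI-18 | Named | Implied by Design |

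**1. Disease activity, between groups.** Two of the three Hypothesis 3 endpoints are named; DAS28 is not. A joint count cannot stand in for it, because tender and swollen joints are two of its four components. The general phrase about secondary measures takes in DAS28, but only in the within-group analysis. A change within a group does not answer a question about yoga compared with controls.

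**2. Disease activity, schedule.**
- At the six-week comparison, blood is available in both arms even under the cytokine paragraph: baseline and end of yoga in the yoga arm, study entry and before yoga in the wait-list arm.
- At two months, the cytokine paragraph gives 0 draws in either arm and Design implies 1.
- The cytokine paragraph cannot be set aside as being about cytokines only, because it ties the listed draws to ESR and disease activity. If it is followed, the ESR is missing at follow-up and DAS28 as defined cannot be computed.

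**3. Pain.**
- The imported model compares baseline with post-treatment between groups, then baseline, post-treatment and follow-up within groups.
- A mean over weeks 1 to 6 is an on-treatment summary and not a post-treatment value.
- Its baseline is not stated. It could be the single current rating or the two weekly ratings taken beforehand.
- The weekly form is scheduled before and during the intervention and control periods, so no matching mean is stated for follow-up.

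**The case against.** **A reader might infer that Hypothesis 3 cannot be tested at all.** The document does not support that. Mood is named in the analysis and measured at each assessment. DAS28 can be computed for the six-week comparison under either draw schedule. Pain has a six-week between-group analysis.

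**A reader might infer that DAS28 has no analysis, or that no patient will have a DAS28 at two months.** Both go too far. The within-group sentence covers DAS28 as a secondary measure. Design implies a follow-up phlebotomy, and the Abstract lists a medical exam among the assessments and gives three collection times. The two-month draw is therefore contradicted, not shown to be absent. Joint counts would be available either way.

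**DAS28 might be called the only objective secondary outcome.** By the protocol's own definition it includes a patient-rated visual analogue scale, so that label does not hold.

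**The weekly mean might be said to dilute the pain effect by a known amount.** If the effect built up linearly, the mean would capture (1+2+3+4+5+6)/6 = 3.5 of 6 units, or 58% of the week-6 effect. The protocol states no time course. With a plateau from week 3 the share is (1/3 + 2/3 + 4)/6 = 83%, and with an immediate effect it is 100%. Averaging also lowers noise. With an assumed equal correlation r between ratings, the SD of a six-rating mean is √((1+5r)/6) of a single rating's SD. Even under linear build-up, the standardised effect is then 0.583/0.645 = 90% of the week-6 value at r = 0.3, and 0.583/0.764 = 76% at r = 0.5. No single dilution figure should be quoted.

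**Averaging weekly ratings is a legitimate summary.** That stands. The fault is that it differs from the defined outcome and has no stated counterpart at follow-up. The Intervention section does mention weekly contacts in connection with yoga classes taken after the programme, so some weekly contact may continue, but no follow-up pain ratings are scheduled there.

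**These are secondary outcomes in an exploratory pilot.** That also stands, and it limits the weight of the point.

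**Conclusion.** The inconsistency is real and should be corrected. Taken literally, Secondary analyses names no between-group test of DAS28 and uses a pain variable that is neither the defined outcome nor repeatable at follow-up. The cytokine paragraph, taken literally, leaves DAS28 incomplete at two months.

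Its size is a matter of counts: one of three endpoints missing from the between-group analysis, one two-month draw in dispute, and one endpoint with two definitions. No loss of power or bias in a stated amount follows. The conclusion rests on the published text alone and assumes that the cytokine paragraph's draw list covers ESR, which is what that paragraph says.

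One limit remains after correction. The wait-list arm is offered yoga at six weeks and the follow-up analysis is within-group, so the comparison with controls at two months lacks a concurrent untreated arm for every endpoint.

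**What to change.** 1. **Reconcile Design with the cytokine paragraph.** Either state that the ESR draw is repeated at two months in both arms, as Design already schedules, with cytokines kept to before and after the intervention; or remove DAS28 from the two-month part of Hypothesis 3.
2. **Name DAS28 in Secondary analyses.** Use it in place of the joint count in the restated hypothesis, and list it with pain and mood in the between-group analysis.
3. **Use one pain endpoint.** Take the current-pain rating from Secondary outcomes at baseline, post-treatment and follow-up.
4. **Keep the six-week weekly mean as a supporting analysis.** Compare it with the two weekly ratings taken beforehand, and say that in the wait-list arm these precede the control period.

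The cost is wording. Nothing is added beyond the assessments that Design already lists.

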#### The specific aims of this research are to

**1**: Determine the feasibility of a six-week twice weekly (12 session) IYP administered in a group format to older adolescents and young adults with RA.

**2**: Compare the impact of IYP on the primary outcomes of functioning and HRQOL to that of a wait-list control group receiving usual care. Functioning will be assessed by two standardized self-report measures, one of general pain-related functioning and the other of arthritis-specific functioning.

**3**: Evaluate the effects of IYP on secondary outcomes of disease activity, pain and mood.

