#### Phase three (18 Months)

In this final phase, IY teachers will administer the IYP using the revised manual to 70 participants who will be assigned to either treatment (n = 35) or usual care control (n = 35). The controls will be immediately assigned to IYP at the end of the control phase (see Figure 2).

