**Figure 3 F3:**
[figure not shown]
**Selected yoga poses**.

Yoga taught in the Iyengar tradition is known for an extensive teacher training program. Iyengar teachers study for at least seven years before being certified to work with students who have therapeutic needs. They must pass several certification tests before an impartial national board. These tests include teaching, performance of poses and breathing techniques, anatomy and therapeutic sequences. Because of this training, IY teachers across the country and around the world can accurately reproduce the IYP in this study.

The proposed IYP will be administered twice a week for 1.5 hours duration per session for 6 weeks. Due to the extensive time commitment required for the IYP, there will be no instructions for home practice, but neither will participants be discouraged from practicing at home. At the end of the 6-week IYP, those participants who ask for referrals to IY studios/teachers in the community will be given a list of referrals. All home practice as well as post-IYP yoga classes will be monitored during the weekly phone calls/e-mails and at the post-treatment and follow-up assessments; the extent of home practice will be evaluated in the analyses for its potential impact on outcome.

Should subjects experience a flare-up during the IYP, the research team will consult with the patient's rheumatologist and a modified version of the IYP will be offered to the subject consisting of restorative poses that do not place strain on the affected joints.

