### Treatment administration

As illustrated in Figure 4, two streams of yoga classes will run concurrently to minimize the overall length of the study and to maximize the likelihood that yoga classes will be convenient for patients' schedules. For example, Stream 1 classes will be held on Mondays and Wednesdays, while Stream 2 classes will be held on Tuesdays and Thursdays. Stream 1 and Stream 2 will comprise the first Wave of patients (Wave 1). Upon the completion of Wave 1, a second wave of patients (Wave 2) will consist of two additional Streams of classes. A make-up class will be scheduled each week for any patient not able to attend their usual session. Thus, all patients should be able to receive the full course of IYP since classes will be run 5 days per week (e.g., make-up classes held on Fridays). We will make note of how many make-up classes each patient attends and test for possible differential effects due to missing regular classes. Patients in the control groups will be given the opportunity to take part in the IYP at the end of the 6-week control period. To increase patient safety and accurate practice of poses, IY classes will hold a maximum of 9 patients.

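### The weekly forms cannot determine how many yoga sessions are needed: every patient is offered the same 12 sessions over 6 weeks, so session count is tied to time on the programme

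*Protocol article*

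**What the plan says.** In the weekly monitoring form paragraph of Exploratory variables, the protocol article says that responses to this form "will be used to determine the minimum and maximum number of yoga sessions needed to produce change". The sentence before it gives the broader purpose, which is to learn how yoga acts on symptoms over time.

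The exposure is fixed elsewhere in the article:

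- The first specific aim is to "Determine the feasibility of a six-week twice weekly (12 session) IYP administered in a group format".
- The Intervention section states that "The proposed IYP will be administered twice a week for 1.5 hours duration per session for 6 weeks".
- Wait-list patients later receive the same programme: "The controls will be immediately assigned to IYP at the end of the control phase" (Phase three).
- The Randomization section allocates patients to yoga or usual care only. It does not allocate a number of sessions.
- Treatment administration adds a weekly make-up class so that everyone can receive the whole course.

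Home practice is neither instructed nor discouraged, and "the extent of home practice will be evaluated in the analyses for its potential impact on outcome" (Intervention). The form is completed weekly for two weeks before the intervention and then weekly in both the intervention and control periods. The section on mediators and moderators calls the analyses of these data exploratory. Its one example is physical activity as a moderator; it gives no method for the number of sessions needed.

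**The concern.** To say how many sessions produce change, patients must receive different numbers of sessions for reasons unrelated to their prognosis, or session number must at least vary separately from elapsed time. Neither holds here. A symptom curve that starts to fall in week 4 could mean that eight sessions are needed. It could equally mean that a few sessions start a process that takes some weeks to show. The data look the same either way.

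The remaining variation comes from who misses classes and who practises at home. Both are decided after randomisation and may be related to how the patient is doing. A reported minimum or maximum would therefore look like a dose finding without being one. The study is meant to inform a larger trial and to produce a standard yoga protocol, so readers could take such a number at face value.

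**Working it through.** **Inputs.** Two sessions per week for six weeks (Intervention); 12 sessions (specific aims); about 28 completers per arm (the paragraph after the exclusion criteria); weekly forms in both arms (Design, Usual care control, Exploratory variables). The article gives no attendance rate, so the rates below are assumptions.

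**Step 1: the plan's own figure.** 2 per week × 6 weeks = 12 sessions. This agrees with the stated 12.

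**Step 2: yoga arm, planned schedule.** Cumulative sessions in week w are 2w: 2, 4, 6, 8, 10, 12. The correlation with week is 1.0. A model with intercept, week and sessions has three columns but rank 2, so the effects of week and session count cannot be separated. Weekly forms also resolve session count only in steps of two.

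**Step 3: add the control arm's weekly forms.** Controls have 0 sessions in every week.

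- Columns intercept, arm, week, sessions: rank 4 of 4. Natural course over calendar time can be separated from what happens under yoga.
- Columns intercept, arm, week, arm × week, sessions: rank 4 of 5. Here arm × week is time on the programme, and sessions = 2 × (arm × week). Session count and time on the programme remain aliased.

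The control arm therefore solves one problem and not the other.

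**Step 4: imperfect attendance.** Attended sessions were simulated for 28 patients over 6 weeks, with each of the two weekly sessions attended at the assumed rate. The variance inflation factor is VIF = 1/(1 − r²), where r is the correlation of week with cumulative attended sessions. Attendance was taken as independent between sessions, then as varying between patients (beta distribution with parameters summing to 10, a within-patient correlation of 1/11 ≈ 0.09), then as strongly clustered (within-patient correlation 0.3).

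| Assumed attendance | Independent: r (VIF) | Mild clustering: r (VIF) | Correlation 0.3: VIF |
|---|---|---|---|
| 95% | 0.985 (34) | 0.976 (21) | about 11 |
| 90% | 0.969 (16) | 0.949 (10) | about 6 |
| 80% | 0.934 (8) | 0.896 (5) | about 3 |

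The collinearity depends strongly on how attendance clusters, and the independent case is the most extreme. It is also the lesser problem. Where the VIF is low, the separation comes entirely from patients who differ persistently in attendance, and that difference was not randomised.

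**Step 5: the upper end.** Programme exposure stops at 12 sessions. A plateau before week 6 could be seen as a feature of the time course. A need for more than 12 programme sessions could not, because further exposure is only self-chosen home practice or community classes.

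**The case against.** The strongest reply is that the sentence follows one about the action of yoga over time. It can be read as asking after how many twice-weekly classes change first appears and by when it levels off. Both can be described within 12 sessions, and the control arm supplies the reference curve. This stands as a description of a time course. It does not rescue the statement as written, which promises to determine the number of sessions needed. The control arm also means that it would be too broad to say that session count cannot be separated from time at all; the aliasing is with time on the programme.

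Several stronger readings are tempting, and the document does not support them:

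- *That this is a main deliverable.* It sits among exploratory variables and is in no aim or hypothesis.
- *That it will fix the session number of the larger trial.* The article says that the study informs a larger trial, but nowhere links this item to that choice.
- *That patients miss classes because they feel worse.* The Discussion names school, work and childcare conflicts, and modified participation is offered during flares. Health-related absence is plausible but not documented.
- *That the plan to "test for possible differential effects due to missing regular classes" is a second dose analysis.* That sentence concerns make-up classes, and a patient who uses them can still receive the full course.
- *That the variance inflation factors show a faulty model.* No model with both week and session count is specified. The factors illustrate how little separate information there is.

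A full analysis plan may exist, but it could not repair this, since the limit lies in the design.

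**Conclusion.** The statement is wrong as written, and the correction is minor. With one 12-session schedule and no randomisation of session number, the weekly forms cannot determine a minimum or maximum number of sessions needed. At full attendance the aliasing with time on the programme is exact. That result needs only the stated schedule and no assumed rate. With attendance of 80% to 95% the VIF runs from about 3 to 34, depending on the assumed rate and clustering; the article supplies neither. That self-selected attendance and home practice cannot support a causal dose statement holds whatever the VIF. The randomised comparison on the primary outcomes is unaffected.

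**What to change.** Delete the claim about the minimum and maximum number of sessions. In its place, state that the weekly forms will be analysed with a group-by-week repeated-measures model over the randomised six-week period, with the two pre-intervention weeks as baseline. Report the yoga-minus-control difference at each week with a 95% confidence interval, described as a time course under a twice-weekly schedule. State also that controls complete the two baseline weeks before their control period, since the text ties those weeks only to the intervention.

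Do not name the first significant week as the dose needed. With six weekly contrasts and about 28 completers per arm, that week would reflect power and multiplicity as much as onset. Label any relation of attendance or home practice to outcome as an exploratory, non-causal association.

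The cost is a change of wording and one model on data already being collected, with no added visits or patients. The downside is that the dose claim is given up.
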